### Blinding

The majority of candidate POCTs considered for this study will generate results automatically without user interpretation. Should user interpretation be required, the sites will be asked to perform the POCTs requiring user interpretation prior to interpretation of the urine dipstick and before any other POCT automatically reports results; ordering of testing and interpretation will be communicated to sites during the training of the POCT. All samples will be tested on novel POCTs by staff who are not aware of the reference standard result and are also asked to disregard the outcome of the novel diagnostics in the clinical management of the patient since the performance of these tests is still unclear. Reference laboratory staff will be blinded to the results of POCTs carried out within primary care clinics.

### Statistics and data analysis

The statistical aspects of the study relating to the analysis of the primary outcome are summarised here, with details fully described in a statistical analysis plan that will be finalised before any analysis takes place.

### Statistical methods

To determine the diagnostic accuracy of multiple POCTs to detect UTI and determine antibiotic susceptibility if applicable (some tests may only provide a UTI diagnosis) for manufacturer defined antibiotic panels, participants will be cross-classified into 2×2 contingency tables according to:

For the case of POCT which incorporate both UTI diagnosis and ASTSamples determined to be UTI positive according to the POCT and organisms detected as resistant to panel antibiotic (yes/no).Samples determined to be UTI positive according to the laboratory reference standard and organisms detected as resistant to panel antibiotic (yes/no).For the case of POCT which incorporate UTI diagnosis onlySamples determined to be UTI positive according to the POCT (yes/no).Samples determined to be UTI positive according to the laboratory reference standard (yes/no).

This information will be used to estimate the sensitivity, specificity, positive and negative predictive values, and positive and negative likelihood ratios for detection of UTI and for the AST where applicable (either phenotypic or molecular), for each POCT. Results will be presented with exact 95% CIs. The differences in the sensitivity and the specificity of the POCT to detect UTI and the corresponding parameters for the urine dipstick will be calculated and presented with 95% CIs. This information will be used to estimate the proportion of samples that would be correctly classified by the POCT but not by the dipstick or vice versa. Results of AST will be presented stratified by organism (as detected by the laboratory reference standard) and antibiotic, with allowance made for organism/antibiotic combinations in which the uropathogen is known to have intrinsic resistance or for which AST is not recommended to be reported in international guidance. AST results will additionally be classified and presented in terms of categorical agreement.

If feasible, for participants whose samples have been tested with more than one comparable POCT (ie, paired sampling), results from the different POCTs will be additionally cross-tabulated against each other. The number of participants prescribed discordant antibiotics will be tabulated and expressed as a proportion of the total, with a 95% CI. These will also be tabulated by the reason for the discordance—for example, an antibiotic prescription without confirmed UTI, or a specific antibiotic being prescribed to an individual for whom the organism was not susceptible to that antibiotic. An exploratory analysis will summarise the baseline symptoms and dipstick results of (1) participants for whom the POCT and laboratory reference test gave discrepant results and (2) participants for whom discordant antibiotic prescriptions were issued. If there are sufficient samples with multiple POCT results available, we will investigate using latent variable methods to simultaneously take account of all results performed on the same sample and quantify any changes of estimates in diagnostic accuracy parameters.^17^

The primary analysis for each POCT assessed will be based on participants’ compatibility with the exclusions of the relevant manufacturer’s IFU and associated Approved Documentation, and a sensitivity analysis will include all participants. The primary analysis will use the laboratory reference standard definition of probable UTI as defined in the details of the reference standard and a sensitivity analysis will use the definition of possible UTI. Another sensitivity analysis will exclude samples detected by laboratory culture to be positive for bacterial species as either the sole or the predominant species where the POCT does not test for this organism. Further sensitivity analyses will be prespecified in the statistical analysis plan.

As most missing test results are likely to be incidental, the primary analysis will use complete-sample data. We will report the test failure rate, with reasons if known, and the proportion of participants who could not be recruited because the time between sample production and analysis is longer than recommended by the manufacturer. To assess whether missing test data biases the diagnostic accuracy assessment,^18^ the distributions of baseline characteristics and POCT results will be compared for individuals with missing results and individuals with non-missing results to check for possible differential patterns of verification. If the proportion of missing data exceeds 10%, we will supplement the primary sensitivity and specificity results with values of the ‘test ignorance region’, that is, the range of sensitivities and specificities that are consistent with the complete data, allowing for non-ignorable missing data.^19^

Where appropriate, results will be presented according to the Standards for Reporting of Diagnostic Accuracy Studies (STARD) guidelines for reporting diagnostic studies.^20^

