The numbers in table 1 refer to the numbers of ‘positive’ samples required. In the case of POCTs that attempt to detect UTI, the total sample size is estimated by dividing the appropriate number in the table by the assumed prevalence of UTI. For example, in the case in which the assumed sensitivity is 99%, the minimum target sensitivity is 90%, and the prevalence of UTI is 30% (0.3), the total number of samples required for 90% power is 64/0.3=213. For tests that perform AST, the total sample size is estimated by dividing by the product of the assumed prevalence of UTI and the assumed proportion of UTI samples that contain a pathogen resistant to the antibiotic(s) of interest. For example, in the case in which the assumed sensitivity is 99%, the minimum target sensitivity is 90%, the prevalence of UTI is 30% (0.3) and the proportion of UTI samples that are trimethoprim-resistant is also 30% (0.3), the total number of samples required for 90% power is 64/(0.3×0.3)=711. These assumptions are informed by previously published data for prevalence of laboratory-confirmed UTI and antibiotic resistance in symptomatic patients in primary care settings.^5^

Any assessment of early-stage POCTs will use an initial pilot that aims to recruit 30 positive samples. For UTI detection without AST determination, this would require 100 samples in total, assuming a prevalence of 30%. In this scenario, the pilot study would be expected to estimate sensitivity with a 95% CI total width of 0.25 (eg, 0.72 to 0.97), and specificity with a 95% CI total width of 0.16 (eg, 0.80 to 0.96), which will inform a decision on the suitability of the POCT to continue to a fully powered diagnostic accuracy assessment.

Up to 900 participants will be recruited based on the information outlined above. The sample size may require an amendment if additional POCTs are to be added.

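### For tests with AST, the 2×2 table as written is a composite of UTI detection and resistance, so its overall figures are not AST accuracy and the primary AST denominator is unclear

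*Protocol article*

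**What the plan says.** In the protocol article, Statistical methods, "participants will be cross-classified into 2×2 contingency tables according to" two axes. For POCTs that combine UTI diagnosis with AST, the index axis is whether a sample is "determined to be UTI positive according to the POCT and organisms detected as resistant to panel antibiotic (yes/no" and the reference axis is whether it is "determined to be UTI positive according to the laboratory reference standard and organisms detected as resistant to panel antibiotic (yes/no". For POCTs that diagnose UTI only, both axes are simply UTI positive, yes or no.

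The section then derives sensitivity, specificity, predictive values and likelihood ratios "for detection of UTI and for the AST where applicable (either phenotypic or molecular), for each POCT". It adds that "Results of AST will be presented stratified by organism (as detected by the laboratory reference standard) and antibiotic", that categorical agreement will also be presented, and that the POCT's sensitivity and specificity for UTI will be compared with the dipstick's.

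Under Sample size, the AST example assumes 99% sensitivity against a 90% minimum, 30% UTI prevalence and 30% trimethoprim resistance among UTIs: "the total number of samples required for 90% power is 64/(0.3×0.3)=711".

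**The concern.** Accuracy of AST is part of the primary outcome. On the table as described, a sample counts as yes only if it is both UTI positive and resistant. Everything else is no, which mixes susceptible UTIs with urines that do not meet the UTI definition.

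Two things follow. Specificity and negative predictive value labelled as AST results are driven largely by samples that say little about AST, and so look better than AST performance in infected samples. Sensitivity labelled as AST sensitivity also carries every UTI that the device failed to detect, so a detection failure cannot be told from a susceptibility error. In addition, a UTI that the POCT misses is scored as a correct no whenever the isolate is susceptible, although no susceptibility result was produced.

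**Working it through.** **Which table the text defines.** The unit is the participant, and no restriction to reference-positive or POCT-positive samples is stated. The UTI-only table uses the same yes/no form over all samples. The AST sample size multiplies prevalence by resistance, with no term for detection by the POCT. Under Index tests, the PA-100 goes on to AST only after bacteriuria is detected, so a POCT-negative sample has no AST result and can enter this table only as no. Together these favour the composite reading.

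**The plan's own figure.** One-sample proportion, normal approximation, two-sided 5%, 90% power:

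n = [(1.960·√(0.90×0.10) + 1.282·√(0.99×0.01)) / (0.99 − 0.90)]² = [(0.588 + 0.1275)/0.09]² = 63.2, rounded up to 64. Then 64/(0.3×0.3) = 711. The same formula reproduces all 18 numbers in Table 1. The arithmetic is right; the question is what the sensitivity refers to.

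**Who is in the reference-no group.** At N = 711, 30% prevalence and 30% resistance:
- resistant UTI: 711×0.09 = 64
- susceptible UTI: 711×0.21 = 149
- reference UTI-negative: 711×0.70 = 498

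The specificity denominator is 149 + 498 = 647, of which 498 (77%) are UTI-negative. At N = 900 it is 630/819, again 77%. With resistance held at 30%, the share is 85%, 68% and 59% at prevalences of 20%, 40% and 50%. At 30% prevalence and 5% resistance it is 71%.

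**Effect on specificity.** Let D be UTI detection, SpU the UTI specificity, SpA the AST specificity among detected UTIs, and q the share of false UTI positives called resistant.

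Composite specificity = 1 − [0.21·D·(1 − SpA) + 0.70·(1 − SpU)·q]/0.91.

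The article gives no values for these. Assume D = SpU = 0.90 and SpA = 0.80:
- q = 0: 1 − 0.0378/0.91 = 0.958
- q = 0.3: 1 − (0.0378 + 0.0210)/0.91 = 0.935
- AST calls made at random (SpA = q = 0.5): 1 − (0.0945 + 0.0350)/0.91 = 0.86

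**Effect on negative predictive value.** An AST that always reports susceptible makes every sample a no, so the composite value is 0.91, against 0.70 among UTI-positive samples. With AST sensitivity and specificity both 0.80, D = 0.90 and q = 0, the composite value is 0.8722/(0.8722 + 0.0252) = 0.97, against 0.56/(0.56 + 0.06) = 0.90 among UTI-positive samples.

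**Effect on sensitivity.** Composite sensitivity = D × AST sensitivity among detected UTIs. With D = 0.90 and AST sensitivity 0.95 it is 0.855.

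**What stratifying by organism changes.** If the strata hold only reference UTI-positive samples and the composite rule is kept, specificity is 1 − D·(1 − SpA) = 1 − 0.90×0.20 = 0.82 against a true 0.80. Most of the inflation goes. The remainder is missed susceptible isolates scored as correct. Sensitivity stays at 0.855.

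**Sample-size example.** If the 99% is AST sensitivity among detected UTIs and D is assumed to be 0.95, composite sensitivity is 0.9405. With 64 positives, the exact two-sided 5% test against 0.90 rejects at 63 or more correct. Its power is 87% at 0.99 and 10% at 0.9405.

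**The case against.** The other side has several fair points.

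- The yes/no can be read as attaching to resistance among UTI-positive samples only. That is possible, but less natural given the parallel UTI-only rows and the prevalence × resistance product. If it was meant, the wording still needs correcting.
- A reader might infer that no UTI-detection accuracy is planned for AST devices. The article does not support that. The composite table cannot supply it, but the dipstick comparison is promised with no exemption for AST devices, so a UTI yes/no table is already implied.
- A reader might infer that AST specificity rests mostly on urines with no organism. That is not supported either. The primary reference is probable UTI, a pure culture at 10^5 CFU/mL or more, so reference negatives include lower counts, mixed growth and possible UTI. How many are organism-free cannot be derived.
- Organism-stratified results and categorical agreement are already planned. Samples with no reference organism have no stratum, so the 77% and the inflated specificities apply to the overall table, not to those displays. This stands and narrows the point.
- The measures are reported together. A device that never reports resistance would show a negative predictive value of 0.91 beside a sensitivity of zero. The composite also lowers sensitivity, which works against the device.
- A composite is a legitimate end-to-end result, and restricting to POCT-positive samples would hide missed resistant infections. Both are true. The fault is in labelling the composite as AST accuracy, and any restricted table must keep the misses in view.
- The statistical analysis plan, not shown here, may settle the denominators. But the article does not leave the table open: it states one.

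**Conclusion.** The concern holds for the overall 2×2. As written, its specificity and negative predictive value pool reference UTI-negative urines (77% of the reference-no group on the article's own 30%/30%) with susceptible UTIs, and its sensitivity is UTI detection multiplied by resistance detection. The size of the distortion depends on device performance that the article does not give. Under the assumptions above, 0.80 becomes 0.935 to 0.958 for specificity, and 0.95 becomes 0.855 for sensitivity.

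The stratified display and categorical agreement limit the harm. They do not redefine the table or say how reference-positive samples missed by the POCT are counted, and they leave two possible AST denominators without naming the primary one.

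It would go too far to say that the study is underpowered or that 711 is wrong. The figure reproduces, the article calls its sample sizes indicative, the fall to 10% power rests on an assumed 95% detection rate, and up to 900 participants would give about 81 resistant UTIs (900×0.09) rather than 64.

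**What to change.** For every POCT with AST, state in the protocol and the analysis plan:

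- (a) A UTI yes/no table against the reference in all evaluable samples.
- (b) For each antibiotic, a resistant/susceptible table against broth microdilution among reference UTI-positive samples with a valid reference AST and a POCT AST readout. Show reference-positive samples without a POCT readout as their own row, split by reference resistance status, so that missed resistant infections stay visible.
- Base AST sensitivity, specificity and categorical agreement on (b), and name it as the primary AST analysis. Keep the composite as a result labelled end-to-end.
- Say whether the 99% in the AST sample-size example is conditional AST sensitivity or the composite. If it is conditional on a readout, the total becomes 64/(0.09×D): about 718, 749, 790 and 837 for detection of 99%, 95%, 90% and 85%, all within the planned 900.

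The cost is wording only, since the data needed are already to be collected. The downside is precision: at N = 711 and an assumed detection rate of 0.90, table (b) holds about 58 resistant and 134 susceptible samples, against 64 and 647 in the composite, so the interval for AST specificity will be wider.

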### Sample size

Sample size requirements for POCTs are based on the estimation of the sensitivity of a POCT to detect reference laboratory culture-confirmed UTI, and key antibiotic resistance markers where applicable. As candidate POCTs may have different levels of diagnostic performance, we present different scenarios, corresponding to sensitivities of 85%, 90%, 95% and 99%. The figures presented here are indicative only and an appropriate choice of sample size may differ, depending on the target performance of the POCT under consideration.

Table 1 relates to testing the sensitivity of the POCT against a fixed target sensitivity, and table 2 indicates the expected precision of the estimated sensitivity for the same range of sample sizes. Test specificity is expected to be estimated with greater precision than test sensitivity, as a majority of samples collected are expected to test negative for UTI.

**Table 1 T1:** Number of ‘positive’ samples required to detect a difference between the assumed sensitivity of the test (rows) and the minimum target sensitivity (columns) with 90% power (first number in each cell) and 80% power (second number in each cell), two-sided test at the 5% significance level

		Minimum target sensitivity		
		0.8	0.85	0.9
Assumed sensitivity of test	0.85	617/471	–	–
	0.9	137/108	471/363	–
	0.95	51/42	96/79	301/239
	0.99	24/21	35/32	64/56

**Table 2 T2:** Expected total width of the 95% CI for the sensitivity, given the sensitivity of test (rows) and the number of ‘positive’ samples (columns)

		Number of positive samples				
		50	100	200	400	600
Assumed sensitivity of test	0.85	0.22	0.15	0.10	0.07	0.06
	0.9	0.19	0.13	0.09	0.06	0.06
	0.95	0.14	0.10	0.07	0.05	0.04
	0.99	0.09	0.06	0.04	0.02	0.02

The numbers in table 1 refer to the numbers of ‘positive’ samples required. In the case of POCTs that attempt to detect UTI, the total sample size is estimated by dividing the appropriate number in the table by the assumed prevalence of UTI. For example, in the case in which the assumed sensitivity is 99%, the minimum target sensitivity is 90%, and the prevalence of UTI is 30% (0.3), the total number of samples required for 90% power is 64/0.3=213. For tests that perform AST, the total sample size is estimated by dividing by the product of the assumed prevalence of UTI and the assumed proportion of UTI samples that contain a pathogen resistant to the antibiotic(s) of interest. For example, in the case in which the assumed sensitivity is 99%, the minimum target sensitivity is 90%, the prevalence of UTI is 30% (0.3) and the proportion of UTI samples that are trimethoprim-resistant is also 30% (0.3), the total number of samples required for 90% power is 64/(0.3×0.3)=711. These assumptions are informed by previously published data for prevalence of laboratory-confirmed UTI and antibiotic resistance in symptomatic patients in primary care settings.^5^

Any assessment of early-stage POCTs will use an initial pilot that aims to recruit 30 positive samples. For UTI detection without AST determination, this would require 100 samples in total, assuming a prevalence of 30%. In this scenario, the pilot study would be expected to estimate sensitivity with a 95% CI total width of 0.25 (eg, 0.72 to 0.97), and specificity with a 95% CI total width of 0.16 (eg, 0.80 to 0.96), which will inform a decision on the suitability of the POCT to continue to a fully powered diagnostic accuracy assessment.

Up to 900 participants will be recruited based on the information outlined above. The sample size may require an amendment if additional POCTs are to be added.

### Embedded qualitative study

#### Aims and objectives

To explore the experiences and perceptions of primary care clinic staff involved in the use of new rapid tests for diagnosing UTI, and how these might affect the feasibility of introducing the tests into primary care settings. To gather information about how the primary care clinic staff view the available tests, how they might implement them as part of consultation for patients with suspected UTI and how this impacts their practice.

### Study design

A qualitative methodology is highly appropriate for capturing and exploring people’s experiences and perceptions of phenomena—in this case, new rapid tests for consultations with women attending primary care for suspected UTI—from the perspectives of the practice staff who will be administering the tests. We will conduct semistructured interviews with the practice staff/trained operators. This method of data collection is well suited to capturing experiences and perceptions and has considerable power to explain actions, decisions and processes. A topic guide will be developed from the existing literature and previous experiences of the research team in conducting such research into point-of-care testing.

A general email will be sent from the TOUCAN Research Team to all the primary care clinics who are taking part in the evaluation of the new tests outlining the embedded qualitative study. Clinicians who have been involved in using the new tests will be invited to take part in the interviews. If they are interested in taking part, they will be asked to contact the TOUCAN research team using contact details given.

When clinicians contact the TOUCAN research team, the purpose of the interview study will be explained and further details will be provided as requested. The information leaflet and the consent form will be sent via email or post as necessary. The clinician will also be informed of the options for timing, location and format of the interview. It is anticipated that all the interviews will be conducted via telephone or through an online platform such as Teams. The clinician will have the opportunity to ask any questions, to receive further information and also to decline any further contact. Clinicians will be informed that they will be able to speak freely at the interview without any negative implications or repercussions on employment. Any clinician who chooses not to participate further in the study will be reassured that this will in no way impact on their current or future working.

If the clinician is happy to proceed, an interview will be arranged. For interviews conducted via the telephone or online, the TOUCAN research team will ensure that participants have read and understood the participant information leaflet, have had an opportunity to have all questions and concerns addressed, and that they are willing to give their consent for the interview to proceed. Verbal informed consent using standardised wording from the informed consent form (ICF) will be captured. In these instances, the researcher will complete the ICF with details of the consent and will securely post/email a copy to the participant for their records.

